### Intervention

The SFP10–14 is a video based programme delivered by trained facilitators that includes parents/guardians and children learning together [26-29]. The 7-week program is delivered over 7-sessions, with 4 optional booster sessions available several months later. The weekly sessions last two to three hours: in the first hour parallel groups of children and parents from up to 15 families develop their understanding and skills, led by parent and child group facilitators; in the second hour, parents and children come together in family units to practice the principles they have learned. The remaining time is spent in logistics, meals and enjoyable family activities. The programme is highly structured with detailed manuals, videos and activities whilst at the same time being highly interactive [26-29].

### Outcome measures

Alongside demographic questions (including family size and structure, parental education, work status, disposable income) we have carefully selected validated instrument measures/scales:

#### Primary outcomes

· Alcohol, cigarette and other drugs: age of first use, lifetime prevalence, 30-days (not other drugs) and 12-month prevalence

· Alcohol use without parent permission

· Drunkenness/binge drinking in past 30 days

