## Background

The European Union (EU) is the heaviest drinking region of the world, drinking 11 litres of pure alcohol per adult each year [1]. More than 1 in 4 deaths among men (aged 15–29 years) and 1 in every 10 deaths among young women in the EU is alcohol related [2]. Young people (aged 15–24 years) are responsible for a high proportion of this burden, with over 25% of youth male mortality and approximately 10% of young female mortality being due to alcohol [1]. Sparse information exists on the extent of social harm in young people, despite the fact that a third of a million (6%) 15–16 year old school students in the EU report engaging in fights, and 200,000 (4%) report unprotected sex, due to their own drinking [1].

Alcohol and other drug use increases markedly between the ages of 11 and 15 years amongst young people in Poland. Between the ages of 11 and 15 the proportion of those who have ever smoked increases from 12% to 59%. At age 11, 10% of 11-year-olds report that they have ever been drunk, and this increases to 53% amongst 15-year-olds. Moreover, 18% of Polish youth report lifetime cannabis use [3]. Early alcohol and other drug use is associated with a range of subsequent adverse health and social outcomes [4-11].

The Strengthening Families Program 10–14 (SFP10-14) is a US-developed family-based intervention for preventing alcohol and other drug use and problems amongst young people. It has been evaluated in two large-scale randomized controlled trials in Iowa, USA [12-16] and has informed the development of a family-based intervention for African American families evaluated in a large randomized controlled trial in rural Georgia, USA [17-19]. Several systematic reviews have highlighted the promising results from these trials but also note the question of whether this US-developed intervention will be applicable in other countries and settings [20-25].

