### Setting and participants

Eligible participants are families with 10–14 year-old children from community settings across Poland. In all families at least one parent should agree to participate. If two children from the same family are involved in the intervention group then both parents will be asked to participate in SFP10-14 group sessions.

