### Analyses

Clustering at the community and family level will be taken account of in multi-level data analysis. Statistical tests of difference in proportions or mean difference tests (or non-parametric equivalents) will be used to examine differences between intervention and control groups. Based on pilot study results [40], data will be analyzed for the whole sample and by several sub-group analyses: child age group (10–12; 13–14); family problems (violence, chronic illness, substance use problems, financial problems etc.; low vs high severity); child behaviour and emotional problems (low vs high severity). All analyses will be on an intent-to-treat basis, and both completed case analysis and multiple imputation analysis will be undertaken.

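### Age of first use, a primary outcome, has a value only for users, so a programme that prevents later starts can appear to lower the age of onset

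*Protocol article*

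**What the plan says.** In the protocol article, Primary outcomes lists for alcohol, cigarettes and other drugs: "age of first use, lifetime prevalence, 30-days (not other drugs) and 12-month prevalence". It neither restricts these to children without use at baseline nor says what value a never-user takes.

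Analyses gives one sentence on how the arms are compared, for all outcomes: "Statistical tests of difference in proportions or mean difference tests (or non-parametric equivalents) will be used to examine differences between intervention and control groups". The same section adds "Clustering at the community and family level will be taken account of in multi-level data analysis" and, on missing data, "both completed case analysis and multiple imputation analysis will be undertaken". It names no time-to-event method, no definition of new use and no adjustment for use at baseline.

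Setting and participants states: "Eligible participants are families with 10–14 year-old children from community settings across Poland". Earlier use is not an exclusion. Background shows that many children in this age range will already have started: ever-smoking rises from 12% at age 11 to 59% at age 15, and ever-drunk from 10% to 53%.

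**The concern.** An age is not a proportion, so of the named tests only a comparison of means or its rank equivalent fits age of first use. The outcome is undefined for a child who has not used by follow-up. A test of the ages that exist is therefore a test among users, a group formed after randomization whose membership depends on the programme.

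Starts before baseline are early and cannot be altered. Starts after baseline are later, and these are the ones the programme is meant to prevent. Each prevented start takes a high age out of the intervention arm's mean. The better the programme works, the lower its mean age of first use, and the result reads as earlier onset.

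The other analysis provisions do not cure this. Multilevel modelling deals with clustering. A complete-case analysis of this outcome is the users-only analysis. Multiple imputation, if it were applied to never-users, would supply ages for events that had not happened.

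At stake is one primary outcome bearing on the fourth stated objective, preventing use. It also bears on the effect that the Discussion credits to the US trials, delayed initiation. Lifetime prevalence has a milder problem: it counts children who had used before baseline, for whom no effect is possible.

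**Working it through.** The article gives no effect size, power or onset figure for these outcomes, so there is no stated result to reproduce. The check asks which way the mean moves, and by how much.

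**Direction.** Let *B* be the share of children who used before baseline (mean onset age *a*₀) and *N* the share who start between baseline and 24 months (mean onset age *a*₁). Among users,

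mean = (*B*·*a*₀ + *N*·*a*₁) / (*B* + *N*).

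Its derivative in *N* is *B*(*a*₁ − *a*₀)/(*B* + *N*)². This is positive whenever some children used before baseline and later starters are older at onset. With *a*₀ and *a*₁ unchanged, a smaller *N* lowers the mean.

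**Round-number example (all inputs assumed).** *B* = 30% with mean onset 10.5 years; new use in 40% of control and 25% of intervention baseline non-users, with mean onset 13.

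- Control: users 0.30 + 0.70 × 0.40 = 0.58; mean (0.30 × 10.5 + 0.28 × 13)/0.58 = 11.71 years.
- Intervention: users 0.30 + 0.70 × 0.25 = 0.475; mean (0.30 × 10.5 + 0.175 × 13)/0.475 = 11.42 years.
- The effective programme looks 0.29 years worse.

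**Model fitted to Background.** Inputs from the article: ever-drunk 10% at 11 and 53% at 15; ever-smoked 12% at 11 and 59% at 15; ages 10–14 at entry; follow-up to 24 months. Assumptions: onset begins at age 8; the onset rate is constant from 8 to 11 and again from 11 onward; baseline age is uniform from 10 to 15; the programme multiplies only the post-baseline rate, by a hazard ratio (HR) of 0.7 or 0.5. The yearly rates are −ln(1 − *p*₁₁)/3 and [−ln(1 − *p*₁₅) + ln(1 − *p*₁₁)]/4: 0.035 and 0.162 for drunkenness, 0.043 and 0.191 for smoking. Results from 2 million simulated children per scenario:

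| | Control | HR 0.7 | HR 0.5 |
|---|---|---|---|
| Drunkenness: mean age among users (years) | 12.06 | 11.92 | 11.80 |
| Drunkenness: lifetime prevalence at 24 months | 47.6% | 42.5% | 38.9% |
| Drunkenness: new use among baseline non-users | 26.5% | 19.4% | 14.3% |
| Smoking: mean age among users (years) | 11.97 | 11.84 | 11.72 |
| Smoking: lifetime prevalence at 24 months | 53.2% | 47.8% | 43.9% |
| Smoking: new use among baseline non-users | 30.3% | 22.3% | 16.5% |

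The share already using at baseline is 28.7% (drunkenness) and 32.8% (smoking). The apparent fall in mean age is 0.14 and 0.26 years for drunkenness, and 0.13 and 0.25 for smoking.

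The formula above confirms the mechanism for drunkenness, where onset before baseline averages 11.27 years in the model and new onset 13.27 (control) or 13.30 (HR 0.5). Control: (0.287 × 11.27 + 0.189 × 13.27)/0.476 = 12.06. HR 0.5: (0.287 × 11.27 + 0.102 × 13.30)/0.389 = 11.80. Almost the whole shift comes from having fewer new starters.

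Two further checks on drunkenness:

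- A pure one-year delay of every post-baseline start still lowers the users-only mean, from 12.06 to 11.93, because delayed starts fall beyond follow-up.
- Restricting the mean to new starters does not rescue it: 13.27, 13.29 and 13.30 years at HR 1, 0.7 and 0.5. Halving the onset rate is nearly invisible.

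**Lifetime prevalence.** The ratio to control is 0.89 and 0.82 (drunkenness) and 0.90 and 0.83 (smoking), at HR 0.7 and 0.5. The matching ratios for new use are 0.73 and 0.54, and 0.74 and 0.55. Power was computed with 300 families per arm (N = 600 at 1:1), two-sided 0.05 assumed, no clustering or dropout, and 300 × (1 − 0.287) = 214 or 300 × (1 − 0.328) = 202 baseline non-users per arm. For unadjusted lifetime prevalence against new use it is 24% against 41% and 57% against 88% (drunkenness), and 26% against 44% and 62% against 91% (smoking).

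**The case against.** The strongest reply is that the article never commits to a users-only mean. Its analysis sentence is generic, does not name age of first use, and allows non-parametric tests. A rank test that places never-users beyond every observed age would qualify and would not reverse. A fuller analysis plan, not shown, may define new use or a censored analysis, and an article may leave such detail to it.

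Part of this stands: the method for this outcome is inferred from the list of tests, not stated. But the article does fix the outcome as primary and does name the kinds of test. Applied in the ordinary way, they give a comparison that can change sign. That goes beyond an omitted detail, and nothing in the text points to the rank-last reading.

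The objection also limits how far the point reaches. Three stronger readings are tempting and are not supported:

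- *Lifetime prevalence is misleading in the same way.* It is not. Compared in all children it is a valid randomized contrast; it is pulled towards no difference and loses power, but does not reverse.
- *The 12-month prevalence asked at the 12-month visit is compromised.* Its window opens at about baseline. The seven weekly sessions cover about 7/52 = 13% of it, the article gives no interval between baseline and the first session, and no material effect has been shown.
- *The trial's overall conclusion would be wrong.* Recent use, use without parental permission and recent drunkenness are also primary and do not depend on age of onset. Even in the example above, lifetime prevalence falls from 58.0% to 47.5%, so benefit would show beside the odd age result.

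**Conclusion.** The point holds for age of first use. With the outcome and test types as written, an effective programme can appear to bring onset forward, by about 0.13 to 0.26 years under the model fitted to the Background figures. The 0.29 years in the round-number example is on the high side: its control-arm new use (40%) exceeds the fitted 26.5% to 30.3%. Its effect, equivalent to HR ln(0.75)/ln(0.60) = 0.56, is weaker than the 0.5 that gives 0.26 years in the fitted model.

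The sizes rest on the assumed onset curve, entry ages and hazard ratios. The direction needs only that some children have used before baseline and that later starters are older at onset, and it was the same in every scenario run.

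For lifetime prevalence the conclusion is narrower: a valid comparison, diluted by use before baseline. The power figures ignore clustering and dropout, so they serve to compare the two measures and do not forecast the trial's power.

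**What to change.** 1. Replace age of first use as a compared primary outcome with initiation: new use by 12 and 24 months among children reporting no use of that substance at baseline. Analyse it with a discrete-time survival model over the two intervals, with a community random effect (and the family level already planned, where a family contributes more than one child). Children with no use by their last visit are censored, not dropped.
2. Report age of first use descriptively only, by arm, with the number of users and the share who started before baseline.
3. Keep lifetime prevalence on the whole sample, with baseline lifetime use as a covariate. Nearly all baseline users will be positive at follow-up, so a plain logistic model may not converge in that stratum; a risk-difference or standardized estimate avoids this.
4. State that never-users are not to be treated as having a missing age in the multiple imputation.

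The cost is wording in Primary outcomes and Analyses. Data are already collected at baseline, 12 and 24 months. The downside is that the initiation analysis uses only baseline non-users, about 67% to 71% of children under the fitted model; the adjusted lifetime-prevalence analysis keeps the whole sample in view.

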#### Secondary outcomes

· General Child Management [30-32]

· Parent – Child Affective Quality [30,32]

· Aggressive and Hostile Behaviors in Interactions [30,32]

· Intervention-targeted Parenting Behavior scale [32,33]

· Index of Aggressive and Destructive Conduct [34,35]

· Family aggressiveness [36]

· Family togetherness [36]

· Maternal support [36]

· Parental monitoring [36]

· Time spent with Mother/Father [36]

· Family Rituals

· Family Life Questionnaire [37]

· Truancy

· School behavior grades

· Grade Point Average

· Strengths and Difficulties Questionnaire [38,39]

· Parental alcohol and cigarette use

### Data collection

Data are collected at baseline, 12 and 24 months. Interview-based questionnaires will be completed by parents and independently by children in separate rooms. In the control group one parent (or both if they express an interest) will complete the questionnaire, and if there are two children in the target age range (10–14) only the youngest will be asked to complete the questionnaire.

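### The youngest-child questionnaire rule is written for control families only; unless intervention families follow it too, control children will be younger and substance-use prevalence will be compared with a bias against SFP10-14

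*Protocol article*

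**What the plan says.** The Data collection section of the protocol article opens with a statement that covers both arms: "Interview-based questionnaires will be completed by parents and independently by children in separate rooms". It then restricts respondents in one arm only. For parents: "In the control group one parent (or both if they express an interest) will complete the questionnaire". For children, in the same sentence, where a family has two aged 10–14: "only the youngest will be asked to complete the questionnaire". No corresponding rule is given for the intervention arm.

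The Setting and participants section shows that families with two participating children are expected there: "If two children from the same family are involved in the intervention group then both parents will be asked to participate". That sentence is about attending group sessions, not about questionnaires.

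The Analyses section says "Clustering at the community and family level will be taken account of in multi-level data analysis", and also "Statistical tests of difference in proportions or mean difference tests (or non-parametric equivalents) will be used" to compare the groups. Child age appears there only as a subgroup factor (10–12 and 13–14).

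**The concern.** Randomizing communities makes the arms comparable only if the children measured are chosen in the same way in each. Here a rule removes the older sibling from measurement in control families, and the text contains no rule that removes the older sibling in intervention families. Followed as written, it makes the age of the measured child depend on the arm.

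This matters because the primary outcomes include lifetime, 12-month and (other drugs excepted) 30-day prevalence of substance use in an age range where use rises fast. A younger control sample would report less use whatever the programme does, so a real benefit could be masked. More families would not reduce this error. A falsely null result would be costly in a trial meant to show whether a US programme transfers to Poland.

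**Working it through.** The article has no figure of its own to reproduce on this point. The check uses its age gradient together with two assumed quantities.

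**Inputs from the document (Background)**
- Ever smoked: 12% at age 11, 59% at age 15. Slope if linear: (59 − 12)/4 = 11.75 points per year. Lifetime cigarette use is a listed primary outcome.
- Ever drunk: 10% at age 11, 53% at age 15. Slope if linear: (53 − 10)/4 = 10.75 points per year. This is illustrative only, because the listed drunkenness outcome refers to the past 30 days.

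**Assumed inputs (not in the document)**
- p, the share of families with two children aged 10–14: 10%, 20%, 30%.
- g, the age gap between them: 2 years.
- Control families contribute the youngest child and intervention families contribute both.

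**Age shift between arms**
- *Form A: only children and sibling pairs have the same mean age m.* The younger of a pair averages m − g/2. Control mean: (1 − p)m + p(m − g/2) = m − pg/2. Intervention mean: m. Difference: pg/2.
- *Form B: only children have the same mean age a as the younger of a pair, and every child counts equally.* Control mean: a. Intervention mean: [(1 − p)a + p(2a + g)]/(1 + p) = a + pg/(1 + p). Difference: pg/(1 + p).

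**Results for ever smoked, g = 2 years**

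| p | Form A: years | Form A: points | Form B: years | Form B: points |
|---|---|---|---|---|
| 10% | 0.10 | 1.2 | 0.18 | 2.1 |
| 20% | 0.20 | 2.4 | 0.33 | 3.9 |
| 30% | 0.30 | 3.5 | 0.46 | 5.4 |

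For example, at p = 30%, form A gives 0.3 × 2/2 = 0.30 years, and 0.30 × 11.75 = 3.5 points. Form B gives 0.6/1.3 = 0.46 years, and 0.4615 × 11.75 = 5.4 points.

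**Wider range.** With p from 5% to 40% and g from 1 to 3 years, the spurious difference in ever smoked runs from 0.3 points (form A, p = 5%, g = 1) to 10.1 points (form B, p = 40%, g = 3).

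**Sensitivity to who is measured in the intervention arm**
- If a two-child intervention family supplies one child at random, its measured child is on average g/2 older than the youngest, and the shift is pg/2.
- If it supplies the older child, the shift is pg.
- If it supplies the youngest, the shift is zero.

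Only the last case removes the difference, and the text confines that rule to the control group.

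**Direction.** In every non-zero case control children are younger, so control prevalence is lowered and the comparison moves against SFP10-14. This applies to the prevalence outcomes. The check does not cover age of first use.

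**The case against.** The best reply is that the decisive fact is inferred. Nowhere does the article say that both siblings in an intervention family complete questionnaires, and the sentence about two children concerns attendance at sessions. This is fair, and it makes the conclusion conditional. It does not remove it: the limit is stated for one arm only, and the age difference vanishes only if intervention families are held to the same rule.

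Several stronger readings are tempting but unsupported:
- *The family-level clustering term shows that siblings are measured.* It does not. Parents and a child from the same family, two parents, or repeated visits would each give several records per family.
- *The mix of mothers and fathers differs by arm.* The parent rule is indeed stated for control only, but both control parents may respond if interested, and the intervention rule for parent questionnaires is not given. Neither the size nor the form of a difference can be derived.
- *Age is the strongest predictor of the outcomes.* The Background shows a steep age trend but compares age with no other predictor.
- *The larger figures are the expected bias.* Form B rests on a particular assumption about the ages of only children and on equal weight per child. If families rather than children are weighted equally, it too gives pg/2, and a family-level model may move the estimate that way.

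It can also be said that baseline data are collected and that covariates belong in an analysis plan that is not shown. That is correct, and the absence of age adjustment from the article is not counted against it. Adjustment could reduce the bias. The arm-specific respondent rule, however, is stated in the article itself and is not a detail left for later.

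**Conclusion.** The point holds in conditional form. The protocol article fixes a child-respondent rule that differs by arm as written. Unless intervention families are also limited to the youngest eligible child, control children will be younger and the prevalence comparisons will be biased against SFP10-14.

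For ever smoked, a plausible size is 1.2–3.5 points, and up to 2.1–5.4 points under the less favourable assumption. Both ranges rest on 10–30% two-child families, a two-year gap, a linear age trend and no age adjustment. The article gives neither the share of two-child families nor the age gap, and the bias is small if such families are few.

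A reader might infer that the primary comparison is already shown to be biased, or that randomization has lost its value. The documents do not support that: the intervention-arm practice is not stated, and a common analysis set can restore the comparison. For parent respondents, all that can be said is that the rule is stated for one arm only.

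**What to change.** State one index-child rule and one index-parent rule, identical in both arms and fixed at recruitment. For instance, the youngest eligible child and one named main caregiver complete the questionnaires that feed the primary analysis. Siblings' and second parents' data can be kept for secondary analysis, preferably collected in the same way in both arms.

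If data have already been collected, define the primary analysis set as the youngest eligible child per family in each arm and adjust for child age. The expected age difference from child selection is then zero. This requires that the youngest eligible child was in fact interviewed in intervention families, so the number of families where that is not so should be reported. Reporting the number of two-child families and the age distribution by arm would also show how much was at stake.

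The cost is one sentence in the protocol and the loss of some intervention-arm sibling records from the primary analysis. Those records are correlated within family, so each adds less information than a child from a new family.
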